Information from participants GP regarding current diagnoses and medication and lab values (blood count, cholesterol, glucose, renal and liver function, thyroid hormones, B12 vitamin, folic acid)	
Other control variables	
Psychological and behavioral eval. II	Perceived Stress (Levenstein et al., 1993) (PSQ), and sleep quality (Pittsburgh Quality of sleep scale).
Use of e-health systems to track health habits	

**Table 3 tab3:** CITA GO-ON study visits assessments.

Variables	Baseline evaluation	Randomization	v1	v2	v3	v4	v5	v6
Time from randomization visit	-12 weeks	0	4 months	8 months	12 months	16 months	20 months	24 months
Visit time window	+/− 30 d.		+/− 20 d.	+/− 20 d.	+/− 20 d.	+/− 20 d.	+/− 20 d.	window of 90 d.
Primary outcomes								
Cognitive performance I	x				x			x
Secondary outcomes								
Cognitive performance II	x				x			x
Functional independence	x				x			x
QoL	x				x			x
Psychological and behavioral eval. I and II	x				x			x
Exploratory variables								
Cognitive performance III	x				x			x
Socioemotional evaluation	x				x			x
Nutritional evaluation I	x				x			x
Nutritional evaluation II	x							x
Physical activity and exercise eval. I	x				x			x
Physical activity and exercise eval. II	x				x			x
PHYSICAL and METABOLIC CONDITION	x				x			x
Brain MRI	x							x
Blood samples	x							x
Cognitive performance IV	x							
Safety variables								
Adverse events evaluations	x				x			x
Information from participants GP regarding current diagnoses and medication and lab values.	x							x
Intervention group-specific variables								
Nutritional evaluation I			x	x		x	x	
Physical activity and exercise eval. I			x	x		x	x	
PHYSICAL and METABOLIC CONDITION			x	x		x	x	

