#### Safety assessments

2.6.4

Participants provide information on past medical history and current illnesses, which is confirmed through their clinical history obtained from their General Practitioners (GPs) at the beginning of the study period and follow-up visits. Any change in a participant health along the study is recorded as an adverse event. Adverse events are actively identified through structured interviews at every follow-up visit. Current diagnoses, medication, and lab values, including blood count, cholesterol, glucose, renal and liver function, thyroid hormones, B12 vitamin, and folic acid, are documented before randomization.

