#### Group 1—RHA group

2.7.2

Participants assigned to the RHA group undergo follow-up evaluations at 12-month and 24-month marks. Adherence to the lifestyle recommendations provided during the randomization visit is self-directed, with no additional guidance on the activities pursued to follow these recommendations. Participants may connect with other healthcare professionals, including their general practitioners, who are not part of the study team according to their individual health needs.

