#### Group 2—MD-Int group

2.7.3

The MD-Int program represents an update of the GZ pilot study intervention program, introducing a socio-emotional component along with a greater frequency of visits and extended materials within each intervention domain. The program aims to promote healthy brain aging, provide tools for incorporating these routines into daily life, and strengthen the social environment. The program is tailored to each participant needs and abilities throughout the study. Apart from the 12-month and 24-month visits participants in the MD-Int group receive individual interviews with the study physician and physiotherapist every 4 months. In these visits cardiovascular and metabolic parameters (blood pressure, pulse, weight, BMI, hip and waist perimeters, capillary glucose, and cholesterol), Mediterranean diet adherence, physical capacity and activity, active medications and adverse events are reviewed and monitored.

The MD-Int program is administered in small groups of 10–15 participants, with a designated investigator or “group leader” overseeing the various MD-Int activities and intervention staff. Intervention components are listed in Table 4. Cognitive stimulation intervention comprises 16 group sessions in workshops (24 h) conducted by a neuropsychologist and over 100 h of individual at-home cognitive training exercises using the EXERCITA® program that was specifically designed after the pilot study. Nutritional and culinary intervention includes eight nutritional and show cooking workshops facilitated by study nutritionists and professional chefs. Individual recommendations for physical exercise based on the VIVIFRAIL©^2^ multicomponent physical exercise tool. And finally, up to 16 group workshops focused on promoting socio-emotional skills the intervention.

**Table 4 tab4:** Description of CITA GO-ON MD-Int components.

Intervention component	Description

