Socioemotional intervention	This branch focuses on emotional well-being by fostering awareness, communication, and regulation of emotions. This is achieved by emphasizing emotional intelligence and the cognitive impact of emotions. This program encompasses six key modules: psychoeducation, emotional awareness, emotional communication, emotional management, coping with loneliness, and promotion of subjective well-being. The intervention will be implemented in 16 group sessions scheduled, along with cognitive intervention workshops. The group work is complemented by a homework assignment designed to integrate the session’s concepts into participants’ daily lives. Socioemotional intervention plays a transversal role in multicomponent interventions, enhancing social commitment, motivation, and adherence to the program.
Cardiovascular risk factor and comorbidities intervention	Every 4 months, the study team will evaluate the participants for cardiovascular risk factor check-ups, including measurements of blood pressure, weight, capillary blood glucose, and cholesterol levels. If the evaluation suggests the emergence of a new risk factor or poor control of a known risk factor, the primary care physician will provide appropriate advice and recommendations for the management, initiation, or adjustment of pharmacological treatments. Additionally, at each visit, the patient’s active medications will be reviewed following the current guidelines for minimizing inappropriate medications from the Basque Public Health System (http://www.osakidetza.euskadi.net/cevime, Vol 20 n° 8, 2012).

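### The text and Table 3 disagree on when adverse events are sought; if the text governs, MD-Int is interviewed six times and RHA twice, and recorded counts are expected to run higher in MD-Int

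*Protocol article*

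**What the plan says.** Section 2.6.4 (Safety assessments) sets the rule for both arms: "Adverse events are actively identified through structured interviews at every follow-up visit". It also defines an AE very broadly: "Any change in a participant health along the study is recorded as an adverse event".

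The number of follow-up visits differs by arm. Section 2.7.2: "Participants assigned to the RHA group undergo follow-up evaluations at 12-month and 24-month marks". Section 2.7.3, in addition to those two visits: "participants in the MD-Int group receive individual interviews with the study physician and physiotherapist every 4 months". At these, among other things, "active medications and adverse events are reviewed and monitored".

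Table 3 gives a different schedule. Its row "Adverse events evaluations" is marked at baseline, v3 (12 months) and v6 (24 months) only. The block headed "Intervention group-specific variables", which covers v1, v2, v4 and v5 (4, 8, 16 and 20 months), lists one nutritional evaluation, one physical activity evaluation and the physical and metabolic measurements. It has no AE row.

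GP records show a similar mismatch. Section 2.6.4 has illnesses confirmed from the GP's clinical history at the start and at follow-up visits. Table 3 marks GP information at baseline and 24 months only.

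**The concern.** Two things follow. First, the document does not settle when AEs are collected: the two text sections agree with each other and Table 3 agrees with neither.

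Second, on the text's schedule the arms are asked a different number of times over different recall periods. Because any change in health counts, many recordable events will be minor and easily forgotten. An arm asked every 4 months will report more of them than an arm asked every 12 months. MD-Int participants also have extra measurements at the interim visits: "Every 4 months, the study team will evaluate the participants for cardiovascular risk factor check-ups" (Table 4). A newly found high reading is itself a change in health and could be recorded as an AE.

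At stake is how the safety data are read. The exercise component is home-based and unsupervised, so a modest excess of minor strains in MD-Int is the sort of signal one would want to interpret. Under unequal ascertainment, such an excess could come from the intervention or from the interview schedule.

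**Working it through.** The document gives no safety sample size, rate or test, so there is no figure to reproduce. The check is a count of contacts, followed by an illustration of size.

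**Contacts after randomization**

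| | MD-Int | RHA |
|---|---|---|
| AE interviews, Sections 2.6.4, 2.7.2 and 2.7.3 | 6 (4, 8, 12, 16, 20, 24 months) | 2 (12, 24 months) |
| Recall period, text schedule | about 4 months | about 12 months |
| AE evaluations, Table 3 | 2 (12, 24 months) | 2 (12, 24 months) |
| Physical and metabolic measurements, Table 3 | 6 | 2 |

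On the text the interview ratio is 6:2 = 3:1; on Table 3 it is 2:2. The measurement asymmetry of 6 v 2 holds on either reading.

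**Illustration of size if the text governs.** Take the same true AE rate in both arms, with events spread evenly over time. Let recall of an event decay by a fraction m per month, so k = −ln(1 − m). Mean detection over an interval of L months is

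D(L) = (1 − exp(−kL)) / (kL).

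The spurious MD-Int/RHA ratio is D(4)/D(12). The values of m are assumptions, not figures from the document.

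| Monthly recall loss m | D(4) | D(12) | Ratio |
|---|---|---|---|
| 1% | 0.980 | 0.942 | 1.04 |
| 2% | 0.961 | 0.888 | 1.08 |
| 5% | 0.904 | 0.747 | 1.21 |
| 10% | 0.816 | 0.568 | 1.44 |

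GP records exist for both arms and shrink this. If they recover a fraction g of events independently of recall, detection becomes 1 − (1 − D)(1 − g). For m = 5% and g = 0.5: MD-Int 1 − 0.096 × 0.5 = 0.952; RHA 1 − 0.253 × 0.5 = 0.873; ratio 1.09.

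| GP capture g (assumed) | m = 2% | m = 5% | m = 10% |
|---|---|---|---|
| 0 | 1.08 | 1.21 | 1.44 |
| 50% | 1.04 | 1.09 | 1.16 |
| 90% | 1.01 | 1.02 | 1.03 |

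The g = 90% row is the plausible one for medically attended events. Low g applies to events that the participant manages alone. The model leaves out any further events found through the interim MD-Int measurements.

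**The case against.** A reader might infer that between-arm safety counts will be biased against the intervention. The document does not support that, for three reasons.

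- If Table 3 is the operative schedule, AE interviews are symmetric and the recall effect disappears.
- No between-arm AE comparison is specified. Section 2.2 lists no safety objective and Section 2.10.5 covers efficacy and secondary outcomes. Tabulation of AEs is commonly left to the statistical analysis plan, which is not shown.
- The size rests entirely on assumed recall. Assuming 90% capture at 4 months and 60% at 12 would give 0.90/0.60 = 1.5. Under the single decay process above, however, 90% at 4 months means k of about 0.054 and about 74% at 12 months, a ratio of about 1.22 before any GP record is used.

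Nor does it follow that real exercise harm could not be distinguished from artefact. Fractures and hospital admissions can appear in GP records for both arms, so the problem is mainly one of minor events.

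It can also be said that Table 3 is merely condensed. It omits the medication review at the interim visits too, although Section 2.7.3 and Table 4 both describe one. That is a fair explanation of the omission, but it makes the text the operative schedule, which is the reading under which the arms differ.

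Finally, the 4-monthly contact is part of the intervention, so some unequal contact is inherent, and the primary cognitive outcome is untouched. Both points are true. They limit the weight of the concern, but the conflict stands, and so does the need for a common basis if AE counts are set side by side. AEs are listed as safety variables and collected in both arms, so readers will naturally compare them.

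**Conclusion.** The conflict is established: Sections 2.6.4 and 2.7.3 put AE enquiry at the MD-Int interim visits, and Table 3 does not. GP-record timing is also inconsistent between Section 2.6.4 and Table 3.

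The consequence is conditional. If the text governs, recorded AE counts are expected to be inflated in MD-Int relative to RHA, mainly for minor, medically unattended events. The direction follows from more interviews, shorter recall and more measurements. The size cannot be derived from the document: the illustrative ratio runs from about 1.0 (little recall loss, or high GP capture) to about 1.4 (10% monthly loss, no GP capture). If Table 3 governs, only the unequal frequency of physical and metabolic measurements remains.

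This affects interpretation of safety, not the efficacy result.

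**What to change.** 1. Reconcile Table 3 with Sections 2.6.4 and 2.7.3, stating for each arm the visits at which AEs are sought and the visits at which GP records are obtained.
2. Record in the eCRF the visit and source of ascertainment for every AE, allowing more than one source per event.
3. Base any between-arm AE comparison on sources common to both arms: the 12- and 24-month structured interviews with the same recall question, and GP records obtained at the same times in both arms. The MD-Int interview must ask about the whole preceding 12 months and log events already noted at an interim visit. Otherwise the restriction would undercount MD-Int.
4. Report events found only at MD-Int interim visits separately, outside the between-arm rates.
5. State as a limitation that some unequal detection remains: the interim interviews may prime recall at 12 and 24 months, and findings from the 4-monthly risk-factor checks can carry into both common sources.

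The cost is a corrected table, a data field and one analysis rule, best fixed before AE data are examined by arm. No visit is added and no event is discarded. The downside is that some interim MD-Int events are reported but do not enter the between-arm rates.

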### Intervention period

2.7

#### Randomization visit

2.7.1

This in-person visit is conducted by the study neurologists, who review medical history, risk factors, cognitive symptoms, functional status, cognitive performance and perform a general and neurological physical exam. Individuals diagnosed with dementia, as defined by the DSM-IV, are excluded. A diagnosis of Mild Cognitive Impairment (MCI) (Petersen, 2004) is confirmed when applicable. Participants are then randomly assigned to the Group 1 or Group 2 to complete the randomization visit. Participants are then informed of their designated group and receive both verbal and written information and recommendations on active and healthy aging, control of risk factors dietary advice, physical activity, social engagement, and routine suggestions aimed at fostering cognitively and affectively stimulating practices.

#### Group 1—RHA group

2.7.2

Participants assigned to the RHA group undergo follow-up evaluations at 12-month and 24-month marks. Adherence to the lifestyle recommendations provided during the randomization visit is self-directed, with no additional guidance on the activities pursued to follow these recommendations. Participants may connect with other healthcare professionals, including their general practitioners, who are not part of the study team according to their individual health needs.

#### Group 2—MD-Int group

2.7.3

The MD-Int program represents an update of the GZ pilot study intervention program, introducing a socio-emotional component along with a greater frequency of visits and extended materials within each intervention domain. The program aims to promote healthy brain aging, provide tools for incorporating these routines into daily life, and strengthen the social environment. The program is tailored to each participant needs and abilities throughout the study. Apart from the 12-month and 24-month visits participants in the MD-Int group receive individual interviews with the study physician and physiotherapist every 4 months. In these visits cardiovascular and metabolic parameters (blood pressure, pulse, weight, BMI, hip and waist perimeters, capillary glucose, and cholesterol), Mediterranean diet adherence, physical capacity and activity, active medications and adverse events are reviewed and monitored.

The MD-Int program is administered in small groups of 10–15 participants, with a designated investigator or “group leader” overseeing the various MD-Int activities and intervention staff. Intervention components are listed in Table 4. Cognitive stimulation intervention comprises 16 group sessions in workshops (24 h) conducted by a neuropsychologist and over 100 h of individual at-home cognitive training exercises using the EXERCITA® program that was specifically designed after the pilot study. Nutritional and culinary intervention includes eight nutritional and show cooking workshops facilitated by study nutritionists and professional chefs. Individual recommendations for physical exercise based on the VIVIFRAIL©^2^ multicomponent physical exercise tool. And finally, up to 16 group workshops focused on promoting socio-emotional skills the intervention.

**Table 4 tab4:** Description of CITA GO-ON MD-Int components.

Intervention component	Description
Cognitive intervention	The targeted cognitive domains include attention, memory, language, executive function, perception, and visual construction abilities. 16 group workshops are distributed over six periods of 3 months throughout the study period. In addition, each participant will receive individually prescribed paper materials tailored to their cognitive status, educational level, and occupation level for cognitive training. These materials are designed to improve each cognitive domain and require a commitment of approximately 20 min of individual sessions three times per week. This initiative promotes cognitive functioning by incorporating cognitively stimulating habits and routines into daily life. Supplementary Figures S1–S3, show examples of routines discussed in the workshops to incorporate them into daily routines.
Physical exercise intervention	The objective is to improve muscle strength/power, cardiovascular endurance (i.e., walking), static and dynamic balance, and flexibility. The program is based on the WHO-recommended material of the VIVIFRAIL© toolkit (http://vivifrail.com/resources/), a home-based multicomponent tailored exercise program that can be implemented during unsupervised sessions with four progressive levels: Disability [A], Frailty [B], Pre-frailty [C], and Robust [D] or advanced fitness level [E-FIT]. The VIVIFRAIL Multicomponent Physical Exercise Program to Prevent Frailty and the Risk of Falls represents an excellent example of an evidence-based program. The VIVIFRAIL physical exercise guide (http://vivifrail.com/resources/) consists of lower-limb, upper-body, balance, and gait re-training exercises.
Nutritional and culinary intervention	The program aims to improve adherence to the Mediterranean Diet through educational workshops and individual counseling sessions. Eight workshops will be held over 2 years, each lasting 1.5–2 h, and are open to cohabitants of participants who do not cook at home. The workshops are conducted by nutritionists and chefs and provide health-related information and culinary education. The program also offers a guide outlining healthy recipes and nutritional information, as well as online and printed resources such as recorded workshops and video recipes to support participants in making healthy lifestyle changes.
Socioemotional intervention	This branch focuses on emotional well-being by fostering awareness, communication, and regulation of emotions. This is achieved by emphasizing emotional intelligence and the cognitive impact of emotions. This program encompasses six key modules: psychoeducation, emotional awareness, emotional communication, emotional management, coping with loneliness, and promotion of subjective well-being. The intervention will be implemented in 16 group sessions scheduled, along with cognitive intervention workshops. The group work is complemented by a homework assignment designed to integrate the session’s concepts into participants’ daily lives. Socioemotional intervention plays a transversal role in multicomponent interventions, enhancing social commitment, motivation, and adherence to the program.
Cardiovascular risk factor and comorbidities intervention	Every 4 months, the study team will evaluate the participants for cardiovascular risk factor check-ups, including measurements of blood pressure, weight, capillary blood glucose, and cholesterol levels. If the evaluation suggests the emergence of a new risk factor or poor control of a known risk factor, the primary care physician will provide appropriate advice and recommendations for the management, initiation, or adjustment of pharmacological treatments. Additionally, at each visit, the patient’s active medications will be reviewed following the current guidelines for minimizing inappropriate medications from the Basque Public Health System (http://www.osakidetza.euskadi.net/cevime, Vol 20 n° 8, 2012).

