### Study objectives

2.2

The primary objective is to ascertain the efficacy of the intervention to attain a 20% reduction in the proportion of subjects exhibiting a decline in cognitive performance, as measured by the change in the global cognition z-score on the modified Neuropsychological Test Battery (mNTB) (Harrison et al., 2007; Kivipelto et al., 2013), between baseline and 24 month visits in the multidomain intervention group (MD-Int) relative to the regular health advice (RHA) group. Secondary objectives include: (1) analyzing the cost-effectiveness of the intervention; (2) determining the beneficial effects of the intervention on functional abilities, quality of life, and symptoms of depression and anxiety; and (3) investigating the impact of lifestyle interventions on: neuroimaging parameters of brain volumetry, white matter integrity and vascular burden; plasma biomarkers of Alzheimer’s pathology, neurodegeneration, and neuroinflammation; epigenetic marks; lipid dysregulation; and cognitive and brain reserve capacity.

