#### Sample size

2.10.1

Sample size calculations were based on the FINGER trial (Ngandu et al., 2015) and GZ pilot study data (Tainta et al., 2024a). Accepting a significance level of 5% and a statistical power of 90% in a one-sided test, 584 subjects would be necessary for each group, with a total of 1,096 participants, to detect a statistically significant difference between the two proportions of participants who decline in performance on the mNTB after 2 years, 49% for the RHA group and 32% for the MI group. The sample size has been calculated to allow a predicted 20% dropout rate according to the GZ study data. In the same way, considering the same level of significance, statistical power, and dropout rate, in order to detect a decline in performance on the mNTB score after 2 years, considering data from the GOIZ ZAINDU Pilot study, we calculated that a sample size of 802 randomized participants would be sufficient to detect by a two tailed Student t test, a difference between groups of 0.10 units in global mNTB score change, considering a 0.33 standard deviation.

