#### Statistical methods for efficacy and secondary outcome analyses

2.10.5

First, the randomness of the samples will be verified to ensure that the baseline characteristics of the two groups do not show statistically significant differences. Univariate analysis will be conducted to identify sociodemographic and diagnostic variables that could differ between the two groups selected randomly before the study.

Continuous variables will be analyzed using Student’s t-test or the nonparametric Mann–Whitney test to compare medians when they do not follow a normal distribution. Categorical variables will be analyzed using the Chi-square or Fisher’s exact test for contrast in each case. Confounding variables will be included in the adjustment for all subsequent analyses. Logistic regression analysis will be performed to the control group and the MD-Int group. Composite scores will be calculated as *Z*-scores standardized to the Baseline mean and standard deviation (SD), with higher scores indicating better performance. The decline will be defined as a decrease in z-scores between Baseline and 24-month visit assessments (Z24month - Zbaseline < 0). Those covariables considered to influence changes in cognition will be introduced as model variables.

Third, mixed models will be used to study the trajectories of the different scores (NTBm) in the control and intervention groups. Mixed models explicitly account for the correlations between repeated measurements within each patient. The factors assumed to have the same effect across many patients are called fixed effects, and those likely to vary substantially from patient to patient are called random effects. In these mixed models, the interaction between the group variable (control vs. intervention) and the time will be included in all final analyses because the study’s final objective is to determine the effect of the intervention on effectiveness along time, adjusted for other variables that could influence them. For statistical analysis, the programs SPSS® (version 23) and R (version 4.2.3 or superior) will be used with a significance level of 95%.

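### MD-Int is delivered in groups and RHA is not, but the sample size has no design effect and the described models place correlation at patient level only

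*Protocol article*

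**What the plan says.** All references are to the protocol article.

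- **Delivery, MD-Int arm** (Group 2—MD-Int group): "The MD-Int program is administered in small groups of 10–15 participants, with a designated investigator" who leads the group. The cognitive component has "16 group sessions in workshops (24 h) conducted by a neuropsychologist and over 100 h of individual at-home cognitive training exercises". For the socio-emotional component, Table 4 says: "The intervention will be implemented in 16 group sessions scheduled, along with cognitive intervention workshops". There are also eight nutrition and cooking workshops. Exercise, home cognitive training and the four-monthly physician and physiotherapist visits are individual.
- **Delivery, RHA arm** (Group 1—RHA group): "Adherence to the lifestyle recommendations provided during the randomization visit is self-directed". No groups are formed.
- **Randomisation** (Allocation): individual, 1:1, stratified by age, sex and MCI.
- **Sample size**: a comparison of two proportions, "Accepting a significance level of 5% and a statistical power of 90% in a one-sided test", with "49% for the RHA group and 32% for the MI group", and a two-sided Student t test for a difference of 0.10 with SD 0.33. Both allow for 20% dropout. No ICC or design effect is given.
- **Analysis** (Statistical methods for efficacy and secondary outcome analyses): logistic regression for decline, then mixed models for trajectories. The only correlation mentioned is this: "Mixed models explicitly account for the correlations between repeated measurements within each patient". Random effects are described as what varies between patients. Delivery group, leader and wave are not mentioned.

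**The concern.** MD-Int participants who share a leader, peers and a long series of workshops may end up with more similar outcomes than participants from different groups. Part of the programme aims at social engagement and adherence through group work, so some positive correlation is plausible. It would arise in one arm only.

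A model that treats those participants as independent then credits the MD-Int arm with more information than it holds. Confidence intervals come out too narrow, the test rejects a true null hypothesis more often than its nominal level, and the planned power is optimistic. A positive trial result could then be challenged on a point that is cheap to settle beforehand.

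**Working it through.** **1. Do the stated sample sizes contain a clustering allowance?**

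Two proportions, n per arm = [z(1−α)·√(2p̄(1−p̄)) + z(power)·√(p1(1−p1)+p2(1−p2))]² / (p1−p2)², with one-sided α = 0.05 and 90% power:
- 49% v 32%, as written: 141 per arm; 141/0.8 gives 177; total 354. This does not reproduce 1,096.
- 49% v 39.2% (49% × 0.8, reading "a 20% reduction in the proportion of subjects exhibiting a decline in cognitive performance" in Study objectives as relative): 437.8, so 438 per arm; 438/0.8 gives 548; total 1,096. This is an exact match, under independence.

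Two means, n per arm = 2(1.960 + 1.282)² × 0.33²/0.10² = 228.9, so 229; 229/0.8 gives 287; total 574. The stated 802 does not reproduce. (The stated 584 per group also conflicts with 1,096, since 2 × 584 = 1,168. That is a separate matter.)

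So the total of 1,096 leaves no room for a design effect.

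**2. Inputs for the clustering check**
- Allocated so far (Results): 465 RHA and 455 MD-Int. After 20% dropout: 465 × 0.8 = 372 and 455 × 0.8 = 364.
- Group size 10–15, midpoint 12.5; evaluable 12.5 × 0.8 = 10. Number of groups: 455/15 to 455/10, about 30 to 46.
- ICC: **assumed** 0.01 to 0.05. The documents give none.

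**3. Standard error and type I error**

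Design effect in MD-Int: DE = 1 + (10 − 1) × ICC.
SE ratio (true/naive) = √[(1/372 + DE/364) / (1/372 + 1/364)].
Actual two-sided level = 2 × P(Z > 1.960/SE ratio); one-sided = P(Z > 1.645/SE ratio).

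| ICC | DE | SE ratio | Two-sided 5% becomes | One-sided 5% becomes |
|---|---|---|---|---|
| 0.01 | 1.09 | 1.022 | 5.5% | 5.4% |
| 0.02 | 1.18 | 1.044 | 6.1% | 5.8% |
| 0.05 | 1.45 | 1.108 | 7.7% | 6.9% |

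For ICC 0.05: (0.002688 + 0.003984)/(0.002688 + 0.002747) = 1.227; √1.227 = 1.108; 1.960/1.108 = 1.769; 2 × 0.0384 = 7.7%.

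**4. Power**, with the MD-Int sample replaced by 364/DE:

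| ICC | 49% v 39.2%, one-sided | 49% v 32%, one-sided | 0.10, SD 0.33, two-sided |
|---|---|---|---|
| 0 | 85.0% | 99.9% | 98.4% |
| 0.01 | 83.6% | 99.9% | 98.0% |
| 0.02 | 82.2% | 99.8% | 97.6% |
| 0.05 | 78.0% | 99.6% | 96.0% |

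For the means at ICC 0.05: SE = 0.33 × √0.006672 = 0.02695; 0.10/0.02695 − 1.960 = 1.75, which gives 96.0%.

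**5. Sensitivity**
- Evaluable group size 8 to 12 (10 to 15 less 20%): the SE ratio runs from 1.02 (size 8, ICC 0.01) to 1.13 (size 12, ICC 0.05), and the two-sided level from 5.4% to 8.3%.
- If 1,096 were randomised, with 10 per group: SE ratio and type I error are practically the same (1.02 to 1.11; 5.5% to 7.7%). Power for 49% v 39.2% falls from 90.0% to 88.9%–84.1%.

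These are normal approximations with equal group sizes, and the same ICC range is applied to the binary and the continuous outcome.

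**The case against.** The strongest reply is that this is largely an argument from silence. The article never lists its random effects. The sentence on repeated measurements explains why mixed models suit longitudinal data, and it does not exclude a term for delivery group. A full protocol or SAP, neither of which is shown, could contain one. Much of the programme is individual, with over 100 hours of home cognitive training against 24 hours in cognitive workshops, and the outcome is each person's own change score rated by blinded neuropsychologists. The ICC may therefore be very small; at 0.01 the standard error rises by only about 2%.

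Much of this stands, and it rules out several stronger readings that a reader might infer:
- **That group membership is fixed for two years.** The article does not say so. Leaders plan each group's later activities, which suggests continuity without proving it, and recorded workshops and video calls may loosen the grouping.
- **That every analysis ignores grouping.** This cannot be shown from an article that does not specify the models fully. The t-test in the methods section follows the baseline comparison and is not clearly an efficacy analysis.
- **That the standard errors are too small as a matter of fact.** This holds only if the ICC is positive, and every ICC used here is an assumption.
- **That clustering leaves the trial underpowered.** At the inputs written in the Sample size section, power stays above 90% up to ICC 0.05. The loss matters only at 49% v 39.2%, a contrast inferred from the objective and from the arithmetic behind 1,096.

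The number finally randomised is also uncertain: 1,051 were selected, and 920 had been allocated when the article was written.

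The reply does not remove the point. The sample-size basis is stated and has no design effect. The analysis text does discuss correlation and locates it only at patient level. Followed as written, the plan understates the standard error for any positive ICC.

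**Conclusion.** The point holds in conditional form. The trial is partially nested by its own description, and neither the sample size nor the described models reflect that. The main harm is to type I error and interval width: with about 10 evaluable per group and an assumed ICC of 0.01 to 0.05, the standard error is understated by a factor of 1.02 to 1.11, and a nominal two-sided 5% test runs at about 5.5% to 7.7%. The effect on power is minor at the written inputs and moderate, from about 85% to 84%–78% one-sided, at the 20% relative reduction. The lower end is close to negligible and the upper end is not, and the documents do not say where the true ICC lies. This should be corrected, but it does not by itself undermine the design.

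**What to change.** 1. Record the delivery-group identifier for each MD-Int participant, and state how changes of group are handled, for example by analysing the group first assigned.
2. In the mixed models, add a random effect for delivery group in the MD-Int arm only, with each RHA participant as a cluster of one. Groups form after baseline and the treatment effect is the group-by-time interaction, so this effect must bear on change during follow-up. A random intercept shared with baseline would not capture it.
3. For the logistic model of decline, use group-robust standard errors with RHA participants as singletons.
4. Report the estimated ICC, and restate power under an assumed ICC range.

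If the full protocol or SAP already has such a term, say so and cite it. The last visit is expected in autumn 2026, so this can be settled before outcome data are compared by arm. The cost is one variable in the dataset, a few sentences of analysis text and slightly wider confidence intervals. If the ICC proves close to zero, almost nothing is lost.
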